## Abstract

**Background:**

Throughout the last decade, tuberculosis (TB) treatment success has not surpassed 90%, the global target. The impact of mobile health interventions (MHIs) on TB treatment outcomes is unknown, especially in low- and middle-income countries (LMICs). MHIs, including interactive voice response technology (IVRT), may enhance adherence and retention in the care of patients with tuberculosis and improve TB treatment outcomes. This study seeks to determine the impact of IVRT-based MHI on TB treatment success (treatment completion and cure rates) in patients with TB receiving care at five public health facilities in Uganda.

**Methods:**

We used a theory-based and human-centered design (HCD) to adapt an already piloted software to design “Call for life-TB” (CFL-TB), an MHI that utilizes IVRT to deliver adherence and appointment reminders and allows remote symptom reporting. This open-label, multicenter, randomized controlled trial (RCT), with nested qualitative and economic evaluation studies, will determine the impact of CFL-TB on TB treatment success in patients with drug-susceptible TB in Uganda. Participants (*n* = 274) at the five study sites will be randomized (1:1 ratio) to either control (standard of care) or intervention (adherence and appointment reminders, and health tips) arms. Multivariable regression models will be used to compare treatment success, adherence to treatment and clinic appointments, and treatment completion at 6 months post-enrolment. Additionally, we will determine the cost-effectiveness, acceptability, and perceptions of stakeholders. The study received national ethical approval and was conducted in accordance with the international ethical guidelines.

**Discussion:**

This randomized controlled trial aims to evaluate interactive voice response technology in the context of resource-limited settings with a high burden of TB and high illiteracy rates. The software to be evaluated was developed using HCD and the intervention was based on the IMB model. The software is tailored to the local context and is interoperable with the MHI ecosystem. The HCD approach ensures higher usability of the MHI by integrating human factors in the prototype development. This research will contribute towards the understanding of the implementation and impact of the MHI on TB treatment outcomes and the health system, especially in LMICs.

**Trial registration:**

ClinicalTrials.govNCT04709159. Registered on January 14, 2021.

## Introduction

The burden and impact of TB on low- and middle-income countries (LMICs) is unprecedented. TB is the leading infectious cause of death worldwide [1]. The disease is one of the leading causes of hospitalization [2] and in-hospital mortality in sub-Saharan Africa [2, 3]. LMICs contribute more than 80% to the global incidence of TB [1]. The high burden in LMICs is mainly attributable to HIV [4], poverty [5], and weak health systems [6]. Despite the high burden, health systems in LMICs are unprepared to contain the epidemic. Adherence and retention in TB programs are low [7, 8], which hampers TB control efforts. Modeling studies suggest that strengthening the TB care cascade could reduce TB incidence by more than 30%. However, there are limited data on the role and impact of mobile health interventions (MHI) in strengthening TB care systems [9].

Mobile phone use and access to the Internet are associated with a reduction in TB incidence and mortality [10]. The impact of mobile health technologies on the enhancement of infectious disease services has been demonstrated globally [11, 12]. The WHO’s “End-TB strategy” emphasizes the use of MHIs to accelerate the implementation and monitoring of TB services [13] and has recommended the application of MHIs to improve adherence to treatment [14]. The rapid growth in the mobile phone industry has transformed health systems across many LMICs [15–17]. Therefore, the increasing mobile phone ownership in LMICs, including in HIV/TB clinics [18, 19], offers an opportunity to strengthen health systems and ensure the delivery of patient-centered care. This may improve patient retention in care and treatment adherence, ultimately improving TB treatment outcomes [20]. MHIs are acceptable to people with chronic infections in several LMICs [21–23], and the infrastructure for their use is improving in many LMICs, including Uganda [24].

The majority of phones used in LMIC are feature phones (non-smart), which are not compatible with the technologies that have been demonstrated to enhance TB care in developed countries [25]. In LMICs, the evidence for the impact of MHIs on TB treatment outcomes is limited to studies involving short message service (SMS) interventions. Although SMS interventions seem to be generally associated with higher treatment success [26], the results from LMICs have been contradictory. Some studies have reported a significant impact on treatment success [12] while others did not find better treatment outcomes with SMS interventions [27–29]*.* The implementation of SMS MHIs is low in LMICs because of high illiteracy and preference for voice-based communication [30–32]*.* Interactive voice response technology (IVRT) delivers voice calls that do not require reading skills. Therefore, IVRT may be acceptable and may have a greater impact. While there is increasing evidence for use of IVRT to optimize care in people receiving HIV care and other health services [33–35], no study has evaluated the impact of mobile-based IVRT on TB treatment outcomes in Africa. We used the information, motivation, and behavioral skills (IMB) model of behavioral change [36] to guide the design of an IVRT-based technology that enhances adherence to TB treatment. The IMB model was initially developed to modify HIV-risky behaviors and has now been adopted to guide behavioral change in developed countries [34]. The model suggests that the motivation of TB patients, increasing adherence skills, and providing information on TB treatment would improve adherence. The model was used to target increase adherence and retention in care since improving these aspects may increase treatment success (Fig. 1).

**Fig. 1 Fig1:**
[figure not shown]
Behavioral change conceptual framework for the study, adapted from Informational Motivation- Behavioral skills model (Fisher, W. A., & Fisher, J. D. (2009))

Owing to the novel approach of IVRT for TB, in this paper, we document our protocol to inform the body of work around the MHI for TB. Furthermore, given the complexity of MHI and its capacity at multiple behavioral levels, we will be undertaking an interdisciplinary study with qualitative, quantitative, and economic components.

### Research objectives

The primary objective of this study is to determine the impact of an IVRT software (CFLU-TB) on treatment success in patients receiving treatment at public facilities in Uganda. The secondary objectives were as follows:
To compare TB cure rates (six months) in patients with microbiologically diagnosed TB in the intervention and control arms.To compare treatment completion (six months) in patients clinically diagnosed with TB in the intervention and control arms.To determine the effect of enhanced TB treatment support with CFLU-TB on retention at 2 and 6 months in patients receiving TB treatment.To assess the perception of patients’ care providers (treatment buddies) and other stakeholders about CFLU-TB.To determine the cost-effectiveness of the intervention.To compare adherence rates between patients in the intervention arm and control arms.To determine the effect of CFLU-TB on adherence to clinic appointments.To compare knowledge about TB/HIV in patients enrolled in the intervention and control arms.To determine Drug-resistant TB rates in the intervention and control arms.To determine the uptake of the CFLU-TB tool in patients and their care providers (treatment buddies).

### Study hypothesis

We hypothesized that IVRT will have a 10% higher impact on treatment success than SMS intervention; therefore, we predict that CFL-TB will lead to a 15%-point increase in treatment success rate in the intervention arm compared to the standard of care (control arm). This is based on a previous RCT that reported 5–9% better treatment success in patients who received SMS adherence reminders versus the standard of care [12, 27].

## Methodology

### Trial design

This study will be an open-label, multicenter RCT involving adult patients with drug-susceptible TB randomized (1:1 ratio) to either the intervention (adherence and appointment reminders, health messages, and 24-h health care worker call service) or control arm. The study will have nested qualitative and economic evaluation sub-studies and a process evaluation to determine the uptake and use of the intervention.

### Study settings

To ensure the generalizability of the results of this study, we planned to enroll patients from several facilities that are representative of typical TB facilities in Uganda. Most patients with tuberculosis [37, 38] are treated at low-level public facilities but a significant burden also exists in urban settings [37, 38]. Therefore, we selected both public and rural TB treatment facilities. Kisenyi Health Center, the first study site, is a large public health center situated within the oldest slum in Kampala which is home to over 23,000 people vulnerable to TB. As a result, the facility receives about 25 new TB patients per month. In addition, Kiryandongo is a rural agrarian district hospital that serves 266,000 people, including 50,000 refugees. The hospital registers an average of 9 new TB cases per month. In contrast, Kasangati Health Center IV is a busy peri-urban facility that serves the Kyadondo East in the Wakiso district and attends to approximately 24 new TB cases per month. To expedite participant accrual, two additional facilities were added to the study protocol version 2.0. Bweyogerere and Kawanda Health Centre IIIs are in the Wakiso district and serve a peri-urban population. They treat approximately 12 patients with TB each per month.

At all health facilities [39, 40], patients with at least one of the dangerous symptoms of TB are offered a sputum GeneXpert test while those unable to expectorate are offered alternative diagnostic tests (CXR, TB LAM, sonography, tissue biopsy, CSF analysis, etc.). Patients with sputum-positive TB are then tested for rifampicin resistance using the GeneXpert MTB Rif assay [40].

### Control arm and the standard of TB care in Uganda

The standard of care at all TB treatment centers follows the national TB treatment guidelines [40]. The standard treatment duration is 6 months, except for patients with TB meningitis and osteoarticular TB who require 12 months of treatment. The standard regimen and duration of treatment for patients with drug-susceptible TB are 2 months for isoniazid, ethambutol, rifampicin, and pyrazinamide, followed by four months of rifampicin and isoniazid [34]. Patients are reviewed every 2 weeks for the first month and monthly thereafter. All patients are encouraged to register a close household or community member to directly observe therapy, but this is not enforced. Patients receive health education during clinic visits with messaging on adherence and treatment completion. At treatment initiation, patients are routinely encouraged to adhere to treatment and appointments, but there are often no patient support systems provided to enhance this. Some patients may use other reminder systems of their choice [41] but this has not been described in patients with TB.

### Description of the proposed mobile health intervention

The technology to be evaluated in this study is Call for Life-TB (CFL-TB^TM)^, a software that is based on open-source mobile technology for community health (MoTeCH) [42]. MoTeCH was initially developed by the Grameen Foundation and the University of Southern Maine with the support of Janssen, the Pharmaceutical Companies of Johnson and Johnson. It was designed as a community MHI platform to improve treatment compliance in patients in LMICs [42, 43]. We then adapted and evaluated the technology to support people living with HIV in Uganda and named it Call for Life ^TM^ (CFL) [34]. CFL-TB uses interactive voice response (IVR) or short messaging service (SMS) to communicate with PLHIV via mobile phones [34]. This prototype, “Call for Life-Uganda”, was iteratively adapted to design CFL-TB, a technology tailored to address the needs of patients with TB. The needs of patients with TB were enumerated through discussions with health workers and patients at IDI HIV/TB clinics. The software was sequentially upgraded, and the subsequent versions were reviewed by end-users at each stage. End-users (study staff and patients with TB) reviewed the software for suitability and suggested changes. Overall, the changes were aimed at optimizing the usability and security of the software. Participants in the intervention arm will receive standard of care plus CFL-TB enhanced TB care, and those in the control arm will receive standard of care.

### The intervention (CFL-TB)

CFL-TB delivers once-daily adherence reminders, pre-appointment reminders, and targeted educative behavior change messages and allows patients to report symptoms to health care workers (HCWs) remotely. As advised by Iribarren et al., participants will decide their preferred language and the timing and frequency of reminders and will ensure that the content is culturally sensitive [44]. The software also delivers calls to registered care providers (buddies) of patients to facilitate daily observed therapy (DOTS), in line with the World Health Organization and Ministry of Health guidelines [14, 40]*.* In Uganda, daily reminders are generally preferred by patients over weekly reminders [8]. To increase adherence to the intervention, if the first call is not answered, the system will make two additional calls, 15 min apart. The study staff will also interview participants in the intervention arm to determine whether they are experiencing any problems. Health care workers enroll patients in the system, monitor the delivery message delivery of messages, and provide ongoing technical support, such as setting personal identification numbers (PINs) and swapping the registered telephone numbers. In contrast, participants are responsible for making and receiving calls. We will synchronize appointment reminders with scheduled appointments, and the software will initiate a call before and on the day of the clinic review. Participants select their preferred time to receive the reminder calls and set their PIN. The system offers short educational messages to increase knowledge about TB/HIV and general health [40]. The CFL-TB software is interoperable with other health information systems used in Uganda, including DHIS2, a web-based database for health reporting.

### Study population and eligibility criteria

This study will enroll adults (≥ 18 years) who were newly diagnosed with drug-susceptible TB (Fig. 2). The detailed eligibility criteria include the following:

**Fig. 2 Fig2:**
[figure not shown]
CONSORT Flow Diagram

#### Inclusion criteria

Evidence of TB diagnosis either confirmed bacteriologically by Xpert MTB/RIF Version G4 assay (Cepheid, Sunnyvale, CA, USA) or clinically diagnosed.Evidence of a personally signed and dated informed consent document that indicates that the participant (or a legal representative) has been informed of all pertinent aspects of the study.Willingness to comply with scheduled visits, treatment plans, laboratory tests, and other study procedures.Aged ≥ 18 yearsMobile phone ownership. Subject to funding, study participants without mobile phones may be provided with mobile phones.Patients who can understand Luganda, Runyankore, Swahili, or English. These languages are the languages spoken by most patients at the study health facilities. If we add Lira RRH as a study site, we will add Luo, the predominant language spoken in the Lango region. Other languages may be added to the service if the anticipated demand surpasses 30 patients.

#### Exclusion criteria

Inability to use a basic feature phone or presence of a clinical condition that interferes with appropriate use of the mobile phone for voice calls (e.g., deafness, severe cognitive impairment)Ongoing participation in another interventional study that the investigator believes will interfere with study procedures or assessment of the outcomes of this study.Patients who are critically ill.Patients with drug-resistant TB (Rifampicin resistant, Multi-drug resistant, and extensive drug-resistant TB).Patients with TB meningitis or osteoarticular TB.Any other clinical condition that, in the opinion of the site investigator, would make the participant unsuitable for the study or unable to comply with dosing requirements.

### Recruitment of study participants and strategies for achieving adequate participant enrolment

This study will recruit from TB clinics within the study clinics. The study staff will identify participants newly diagnosed with TB. To expedite participant accrual, two additional facilities have been added to the study protocol version 2.0. Bweyogerere and Kawanda Health Centre IIIs are in the Wakiso district and serve a peri-urban population. They receive an average of 13 and 10 patients with TB per month (approximately 156 and 120 patients per year, respectively). Additionally, study initiation meetings have been conducted with health facility staff and patients at all study sites study to increase awareness about the study. We hope this enhances the referral of participants to the study.

### Randomization, blinding, and allocation concealment

At baseline, participants will be randomly assigned (1:1 ratio) to either the intervention or control arms (Fig. 2). The study statistician generated study allocation slips for participants for each study site using and these are then enclosed in sealed opaque envelopes. The number of cards allocated per study site will be equal to the enrolment target assigned to the study site. The allocation slips will indicate either the intervention or the control arm. The study arm will be allocated by drawing one envelope by a participant from a closed envelope box. Patients will randomly pick and open an envelope and they will be allocated a study arm that is indicated on the enclosed card. Since the opaque envelopes will be used and drawn from a closed opaque box, the allocation sequence is concealed from the recruiting study staff. We will maintain screening and enrolment logs at each study site to ensure that there is no bias in randomization and enrolment. Due to the study design involving voice reminders to participants, it is not possible to blind participants. However, the analyzing statistician will be blinded to the allocated arms.

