### Data collection

At baseline, the staff will obtain sociodemographic data (age, sex, marital status, level of education, employment status, income, transport costs, distance from the facility) and data on TB infection (method of diagnosis, site of infection, and rifampicin resistance at baseline). Prospectively, data will be obtained on adherence, symptoms, sputum tests, missed appointments, and clinic visits (Table 1). Participants will also be interviewed on phone call costs, hospitalization, and over-the-counter treatments. At baseline, we will interview patients (qualitative data) on their anticipated challenges in the use of IVRT and anticipated benefits and challenges. At months 2 and 6, qualitative data will be collected on acceptability and experience with the digital intervention. We will determine the sputum conversion rate at 2 months and cure at 6 months. Chest radiographs will be used to determine the cure for patients with clinical TB. TB cards and treatment registers will be reviewed for death, adherence, and date of patient visits. We will use micro-costing to obtain data on the direct and indirect costs.

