### Sample size determination

Based on results from a randomized controlled trial in Kenya that demonstrated a 9% increase in TB treatment success following the use of SMS [12], we hypothesize that the interactive voice response platform will lead to at least a 6% higher impact as compared to SMS reminder treatment success (i.e., a 15%-point difference compared to the control arm). A retrospective cross-sectional study of routine data on HIV/TB co-infected patients from the Uganda National Tuberculosis and Leprosy Program reported lost to follow-up rates of 3.5% and 16.6% in urban and rural settings, respectively [7]. The rate of lost-to-follow at the three TB clinics was approximately 11.8%. Therefore, assuming an 11.8% lost-to-follow-up rate, this study would require a minimum of 274 (137 patients per arm) patients to demonstrate a 15% increment in treatment success with a power of 0.8 and precision of 0.05.

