### Analysis of the primary endpoint

We will use logistic regression to determine the crude and adjusted odds ratios of treatment success in the intervention arm versus the control arm. The multivariable model will adjust just for potential confounders, including age, sex, employment status, bacterial load at baseline, TB category, and HIV status [7, 48, 49]. The stepwise backward elimination method will be used to fit the final model. The model with the lowest Akaike information criterion (AIC) statistic will be considered the best fitting. Covariates with a global/trend *p* value > 0.2 at the bivariate analysis, will be adjusted for in the final multivariate model. We will explore factor interactions, including the interaction between age adherence and sputum smear results at baseline. Where interaction is confirmed, we report both the main and interaction effects.

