### Analysis of quantitative endpoints

Logistic regression will be used to determine the adjusted odds ratio for TB cure and treatment completion in the intervention arm versus control arms. We will also determine the predictors of TB cure overall and in both arms. The final model will adjust for age, sex, bacterial load, HIV status, TB site, and symptoms at baseline. We will also determine and compare attrition in the two study arms using the Cox proportional hazards model. We will compute the crude and adjusted hazard rates of attrition in the intervention and control arms. The log-rank test will be used to test for differences in attrition between the study arms. Tests for the Cox proportional hazard assumption will be done graphically using Schoenfeld residuals. The model will adjust for age, sex, Karnofsky score at baseline, HIV status, transport costs, distance from the health facility, TB site, and socioeconomic covariates.

We will compare the mean adherence rates (proportion of TB medicines taken as evidenced by TB card) at 6 months in the intervention and control arms. We will treat adherence as a continuous covariate and compare the median adherence between the intervention and control arms. To compare appointment keeping, we will use ordinal logistic regression to determine the adjusted odds ratios of missed, late, and prompt visits (early used as a reference group). In the sensitivity analysis, Poisson regression will be used to compare the number of missed visits and treatment doses in the intervention and control arms. The models will adjust for age, sex, employment, distance from the health facility, and HIV status. We will use chi-square to compare the proportions of patients with MDR-TB between the two study arms. Additionally, logistic regression will be used to determine the crude and adjusted odds ratios of MDR-TB in the intervention and control arms. Finally, as a proxy for the uptake of intervention and fidelity, we will determine the proportions of successful and dropped and received calls at three different (2, 4, and 6 months) to determine patient exposure and acceptance of the intervention through the study treatment period.

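### Allocation is prepared separately for each of the five sites, but study site is in none of the listed analysis models: a minor loss of precision that costs almost nothing to repair

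*Protocol article*

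**What the plan says.** The section on randomization states that the statistician "generated study allocation slips for participants for each study site", and adds: "The number of cards allocated per study site will be equal to the enrolment target assigned to the study site". Participants draw an envelope from a closed box, and the allocation ratio is 1:1. The article does not use the word, but this is stratification by site.

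The analysis sections name covariates model by model:

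- **Primary logistic model:** potential confounders, "including age, sex, employment status, bacterial load at baseline, TB category, and HIV status". Selection follows: "The stepwise backward elimination method will be used to fit the final model", together with a bivariate p-value screen and AIC.
- **Cure and completion:** "The final model will adjust for age, sex, bacterial load, HIV status, TB site, and symptoms at baseline".
- **Attrition (Cox):** a longer list with transport costs, distance to the facility and *TB site*, but no facility term. No stratification is stated for the log-rank test.
- **Adherence and appointments:** age, sex, employment, distance and HIV status.
- **Stratified analyses (Sensitivity analysis):** HIV status, TB type and gender.

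The Data collection section lists, among the baseline data on TB infection, "method of diagnosis, site of infection, and rifampicin resistance at baseline". *TB site* in the models is therefore most naturally the anatomical site.

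The sample size section cites "lost to follow-up rates of 3.5% and 16.6% in urban and rural settings, respectively".

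**The concern.** When allocation is balanced within sites, the between-site part of the outcome variance cannot contribute to the difference between arms. An analysis that ignores site still counts that part in its standard error, so intervals are somewhat too wide and the test somewhat too cautious.

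Second, drawing from a box guarantees balance at a site only once the box is empty. Two sites were added to speed accrual, and 123 of 274 participants had been enrolled by 15 May 2021, so some sites may stop short of target. A model without site does not correct any imbalance that results.

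There is reason to think sites may differ. They were chosen as an urban slum clinic, a rural district hospital and peri-urban centres. The primary denominator is everyone enrolled, so loss to follow-up lowers success directly.

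**Working it through.** **Plan's own figures.** The plan gives no figure for the effect of site. Its total of 274 is used below only as a size. The sample size section states no control success rate, so 274 cannot be reproduced from its inputs alone. Assuming 0.70 versus 0.85 gives 121 per arm, 121/(1 − 0.118) = 137.2, rounded up to 138, total 276. This does not bear on the present point.

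**Inputs.** Monthly volumes are 25, 9 and 24 (Study settings) and 13 and 10 for the two added sites (Recruitment), total 81. Scaled to 274 with even numbers, the sites have 84, 30, 82, 44 and 34 participants. The rural hospital is the second, 9/81 = 11% of volume. Site success rates are assumptions.

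**Standard error.** With site weights w and success rates p, and p̄ = Σwp, the ratio of the unadjusted to the site-stratified standard error is √[ p̄(1 − p̄) / Σ w p(1 − p) ].

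- Rural site 0.62, others 0.75: p̄ = 0.736; √(0.1944/0.1928) = 1.004.
- Moderate spread (0.80, 0.60, 0.72, 0.70, 0.75): p̄ = 0.732; √(0.1962/0.1927) = 1.009.
- Wide spread (0.85, 0.45, 0.75, 0.60, 0.70): p̄ = 0.718; √(0.2027/0.1869) = 1.041.

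Five evenly spaced rates over 55 to 75% give an excess of roughly 1%, and over 50 to 80% roughly 2 to 3.5%, depending on which sites are low.

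**Type I error and power.** Simulation with 100,000 runs per scenario, exact 1:1 within site, two-sided 0.05, comparing a pooled two-proportion test with a site-stratified Mantel-Haenszel test; power is for a gain of 15 points:

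| Assumed site rates | Type I error, unadjusted / stratified | Power, unadjusted / stratified |
|---|---|---|
| All 0.73 | 5.1% / 5.2% | 89.3% / 89.1% |
| Rural site 13 points lower | 4.9% / 5.0% | 89.8% / 89.8% |
| Moderate, 0.60 to 0.80 | 4.9% / 5.1% | 89.7% / 90.0% |
| Wide, 0.45 to 0.85 | 4.2% / 5.1% | 88.9% / 90.8% |

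In the wide case, adding 15 points takes one site to 100%, so that row is an extreme. These tests stand in for the planned logistic model. There, adding site also changes the odds ratio to one conditional on site, so the effect on the test carries over better than the exact standard error ratio.

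**Imbalance at a site that stops early.** No site targets are given. Suppose a box of 30 + 30 cards (equal numbers inferred from the 1:1 ratio) is abandoned after 30 draws. The hypergeometric 2.5th and 97.5th percentiles for the intervention arm are 11 and 19. Take the extreme split of 19 to 11, and let that site differ from the rest by the whole cited gap, 16.6 − 3.5 = 13.1 points. The arm difference then moves by (19 − 11)/137 × 13.1 = 0.8 points. Its standard error, with success assumed at 0.71, is √(2 × 0.71 × 0.29/137) = 5.5 points.

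**The case against.** The strongest reply is that the primary covariate list is open, that the article promises to control for confounders in all analyses, and that the full protocol or an SAP could add site in a line. It is true that nothing forbids site. But the article does not leave covariates to a later document: it names them for each model and sets a selection rule. Under that rule, a site term added later to the primary model could be removed again. The way the set is fixed is open to comment.

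A second reply is that the harm is close to nil, and this largely stands. With a 13-point rural deficit, power is the same to one decimal. The two harms also do not simply add: emptied boxes leave nothing to correct, while part-full boxes weaken the balance that makes the unadjusted standard error too large.

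Third, a reader might infer from the 3.5% and 16.6% figures that these five sites have very different loss rates. The documents do not support that. The figures are routine data on patients with both HIV and TB, the three original clinics have one pooled figure of 11.8%, and only one site is described as rural. The figures only suggest that sites may differ. Distance and transport costs in some secondary models are at most partial stand-ins for site, and neither is in the primary list.

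**Conclusion.** The point holds as a minor one. Randomisation is stratified by site, and no listed model or stratified analysis includes study site. The resulting analysis is valid and, if sites differ, slightly conservative: a standard error about 1 to 2% too large under moderate assumed spreads, type I error of 4.9% with a 13-point rural deficit and 4.2% with a 45 to 85% spread, and a power loss from nil to about 2 points. All of this rests on assumed site success rates and on enrolment in proportion to the stated volumes.

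Two stronger readings should be avoided. Omitting site does not inflate the false-positive rate; the calculations show the opposite direction. Nor is imbalance at an unfinished site a bias: it is chance variation within what the confidence interval covers, worth under about 1 point in the example, which itself assumes a target of 60 stopped at 30.

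**What to change.** Include study site (five levels) as a forced fixed effect in the logistic models for treatment success, cure and completion and in the adherence and appointment models. Exempt it explicitly from the bivariate p-value screen, backward elimination and AIC; otherwise selection could remove it. Stratify the Cox model and the log-rank test by site. The cure and completion analyses each use only part of the sample, so some sites may contribute few patients; fix any rule for merging small sites in advance and blind to arm. State that *TB site* means the anatomical site of disease.

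The cost is a few lines of text and at most four degrees of freedom per model. Site should be known for every participant, because allocation is done by site, and the sample size stays at 274.
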